##### Patient and informal caregiver questionnaires

Quality of life of the patient will be measured with the use of the European Organisation for Research and Treatment of Cancer Quality of Life Questionnaire (EORTC QLQ C30) and the McGill Quality of Life Questionnaire (MQOL) [17–19]. The MQOL has been selected because it addresses the existential aspects of quality of life as well as the physical, emotional and social aspects of quality of life. A recent review qualified both its content and construct validity as high [20]. The mood of the patient will be measured by two instruments: the Hospital Anxiety and Depression Scale (HADS) and the Patient Health Questionnaire 9 (PHQ-9) [21–24]. Illness-understanding will be measured by a forward-backward translation of the questionnaire developed by the researchers of the previously mentioned study of palliative care for patients with metastatic non-small-cell lung cancer [4]. Data on mood, quality of life, illness understanding and satisfaction with care of the informal caregivers will be obtained by self-assessment instruments: HADS, PHQ-9, the Short Form-36 Health Survey (SF-36) a questionnaire for illness understanding and by the FAMCARE respectively [25]. A forward-backward translated and tested version of the FAMCARE will evaluate the satisfaction with care of the informal caregivers [26].

The surveys filled out by patients and informal caregivers, their frequency and the timing of completion are detailed in Table 3. The patient will complete the baseline questionnaires before randomization and the follow-up questionnaires with regard to quality of life, mood and illness-understanding firstly after 12 weeks and thereafter every six weeks. Change from baseline to 12 weeks after inclusion is chosen because approximately 80 % of patients are expected to be alive at 12 weeks after inclusion [4]. The informal caregivers will complete the baseline questionnaire before randomization and the follow-up questionnaires firstly after 12 weeks and then every six weeks. If the patient dies the informal caregiver is asked to fill out the questionnaire once more 12 weeks after the death.

**Table 3 Tab3:** Types of patient and informal caregiver questionnaires and frequency and timing of completion

	Week					
	Baseline	12	18	24	…	12 weeks after patient’s death
PATIENT FORMS						
EORTC QLQ C30 and MQOL	X	X	X	X	X	
PHQ-9 and HADS	X	X	X	X	X	
Illness-understanding Questionnaire	X	X	X	X	X	
INFORMAL CAREGIVERS FORMS						

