#### Statistical analysis and sample size calculation

To compare baseline characteristics and study outcomes for patients between groups, Fisher’s exact tests, chi-square tests and the independent-samples t-test or the non-parametric equivalent Mann–Whitney *U* will be used. The effect of early palliative care on the primary outcome quality of life will be assessed by multivariate regression analyses adjusting for baseline scores. Survival analysis, i.e. Kaplan-Meier and a Cox proportional hazards model, will be used to examine the effect of systematic early integration of palliative care on the secondary outcome survival from the time of inclusion adjusting for demographic and clinical baseline characteristics. With regard to missing data, we will use the conservative approach of carrying the last observation forward for all missing data.

To detect a significant and meaningful difference in the change of the EORTC QLQ-C30 from baseline to 12 weeks, 118 patients are needed. With the proposed sample size of 59 for the two groups, the study will have a power of 80 % to yield a statistically significant result. This computation assumes a mean score difference of 12 and the common within-group standard deviation is 23.0. A difference of 10 points on the multi-items scales from 0 to 100 is considered meaningful (50;51). On the basis of the study on early palliative care in advanced lung cancer patients, it can be expected that approximately 80 % of the study participants will still be alive at 12 weeks after inclusion and drop-out for reasons other than death will amount to 15 % [4]. In other words, an overall drop-out rate of 35 % is to be expected, accounting for the planned inclusion of a total of 182 patients in the study.

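### At week 12, last observation carried forward means baseline carried forward: about 35% of patients, the dead included, get zero change, and the rule is not assured to be conservative

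*Protocol article*

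**What the plan says.** All references are to the protocol article.

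- *Statistical analysis and sample size calculation* gives the missing-data rule: "we will use the conservative approach of carrying the last observation forward for all missing data". It makes no exception for death.
- The same section sizes the trial on a "difference in the change of the EORTC QLQ-C30 from baseline to 12 weeks, 118 patients are needed". It "assumes a mean score difference of 12 and the common within-group standard deviation is 23.0", and treats 10 points as a meaningful difference.
- It expects that "approximately 80 % of the study participants will still be alive at 12 weeks after inclusion" and that "drop-out for reasons other than death will amount to 15" per cent, and adds the two losses: "an overall drop-out rate of 35 % is to be expected". This takes 118 up to 182 patients.
- The primary outcome is analysed by regression adjusted for the baseline score.
- *Patient and informal caregiver questionnaires* sets the timing. "The patient will complete the baseline questionnaires before randomization", and the follow-up forms come "firstly after 12 weeks and thereafter every six weeks". Table 3 of the article shows no patient form between baseline and week 12.

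**The concern.** The rule and the visit schedule have to be read together. With nothing measured between baseline and week 12, a patient without a week-12 form has only one earlier score. Carrying it forward asserts that this patient's quality of life did not change. For a patient who has died, it enters a pre-randomization score as a week-12 outcome. A living patient who misses week 12 but answers at week 18 is also recorded as unchanged.

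This is a rule the article fixes, not a detail left open, and on the plan's own figures it would supply about a third of the primary-endpoint values. At stake are the size of the reported effect and, if losses differ by arm, whether a difference appears or disappears because of the imputation. Unequal losses are plausible: survival is itself a secondary outcome, and the Discussion of the article says that participants and staff are not blinded.

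**Working it through.** **Inputs from the article:** difference 12, SD 23.0, power 80%, 59 per group, 20% dead and 15% other loss by week 12, 182 patients randomized 1:1 (91 per arm), meaningful difference 10. The significance level is not stated. Two-sided 0.05 is assumed because it reproduces the stated size.

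**1. The plan's own figures.** A two-sample t-test with 12/23, two-sided 0.05 and 80% power needs 58.6, so 59 per arm and 118 in total. Power at 59 per arm is 80.2%. Then 118/0.65 = 181.5, so 182. All of these reproduce.

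**2. How many values are imputed.** 0.35 × 182 = 63.7, about 64 patients: 0.20 × 182 = 36.4 deaths and 0.15 × 182 = 27.3 other losses. If the 15% applies to survivors only, the loss is 1 − 0.80 × 0.85 = 32%, about 58 patients.

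**3. Formula.** Suppose a share m of an arm is missing and set to zero, and observed patients have mean change μ and SD 23. For unadjusted change scores:

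- arm mean = (1 − m)μ
- arm variance = (1 − m)(23² + μ²) − [(1 − m)μ]²
- SE of the difference = √[(variance₁ + variance₀)/91]

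**4. Equal missingness, true difference.** The 12 points are assumed to hold among observed patients, as sizing on evaluable patients implies. The estimate becomes 0.65 × 12 = 7.8 (0.68 × 12 = 8.2 at 32% missing). With observed changes of 0 and −12, the SD falls from 23 to 18.98, the SE is 2.81, and power at 91 per arm is 79%. The loss is in the size of the effect, not in power.

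**5. Unequal missingness, no true difference.** The declines and the gaps are assumptions; the article gives neither. Bias = common decline × gap in missingness, in favour of the arm with more missing data.

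| Common decline | Missing 40% vs 30%: bias, rejection | Missing 45% vs 25%: bias, rejection |
|---|---|---|
| 5 | 0.5, 5.4% | 1.0, 6.5% |
| 10 | 1.0, 6.4% | 2.0, 10.9% |
| 15 | 1.5, 8.0% | 3.0, 17.5% |
| 20 | 2.0, 9.9% | 4.0, 25.5% |

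For example, 15 × (0.45 − 0.25) = 3.0 with SE 2.94 gives 17.5% rejection instead of 5%. Swapping the missing rates reverses the sign. With equal missingness, rejection is 5% at every decline.

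**6. Baseline adjustment.** It does not remove the bias, because the imputed outcome equals the covariate. Simulating the adjusted regression for the 15-point, 45% vs 25% case gave a bias of 3.1 and 20.6% rejection.

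**The case against.** The strongest defence is that the rule really is conservative in the cases the authors had most reason to expect. With equal losses it pulls the estimate toward zero and keeps the type I error. If the intervention prolongs survival, as the Background reports for the lung cancer trial it cites, the control arm has more deaths. With declining scores the rule then favours control. For observed changes of 0 and −12, with 25% missing under intervention and 45% under control, the estimate is 0.75 × 0 − 0.55 × (−12) = 6.6 instead of 12. A false positive for the intervention needs declining scores with more missing data in the intervention arm, or improving scores with more in control. Nothing in the article predicts either.

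That stands as far as it goes. It shows that the rule can be conservative for the test of benefit, not that it must be. An estimate cut from 12 to 7.8 or 6.6 is still a poor answer to how large the effect is.

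Four stronger readings are tempting and are not supported:

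- *The primary result is biased whatever happens.* False differences under the null need unequal missingness together with a mean change other than zero.
- *The standard errors must be wrong because imputed values are treated as observed.* In 6,000 simulated trials of the adjusted regression (assumed SD 23 at each visit, correlation 0.5, missingness unrelated to scores) with 35% missing in both arms, the mean model SE was 2.73 against an empirical 2.72. At 45% vs 25% missing it was 2.72 against 2.70. The fault lies in what is estimated.
- *The rule contradicts the sample size.* Sizing on 118 evaluable patients and analysing 182 is not a numerical conflict, and power stays near 79%. What remains is a mismatch between the effect assumed and the effect estimated.
- *Missing bereavement forms would be filled with caregivers' pre-death scores.* The section describes no caregiver analysis, so this is speculation.

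**Conclusion.** The point holds, and the rule needs to be replaced. On the article's own schedule and loss figures, about 64 of 182 patients (58 on the 32% reading) receive a week-12 change of zero, including about 36 who have died.

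The dilution from 12 to 7.8 assumes equal losses and that the 12 points refer to observed patients. If the trial's planning assumption came true, it would report an effect smaller than the one the article itself calls meaningful.

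The type I error range of about 5% to 25% rests on assumed declines of 5 to 20 points and gaps of 10 to 20 percentage points. It shows what could happen and does not forecast this trial. It is enough to show that the description as conservative is not assured, and that the rule could hide a benefit or create one.

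**What to change.** Delete the carry-forward sentence, including the word *conservative*, and replace it with three statements.

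1. Observed QLQ-C30 scores are analysed with a likelihood-based longitudinal model using the visits already scheduled, adjusted for baseline and department, with the week-12 contrast as primary. A patient who misses week 12 but answers at week 18 then contributes what was measured.
2. Death is handled separately from other missing data. No quality-of-life value is assigned after death, and the week-12 contrast is reported and read together with deaths by arm. The model alone does not settle the matter, because it implicitly extrapolates the course of patients who have died.
3. Two sensitivity analyses are added: one ranking death below any observed score, and a delta-adjusted analysis for drop-out other than death.

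The cost is a change of wording and slightly more analysis work, with no new data and no new patients. The drawback is reliance on a missing-at-random assumption for drop-out other than death, which the delta-adjusted analysis examines.

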#### Ethical considerations

Since the participants in the control group will receive extensive medical and paramedical care and will not be refused palliative care at their request, it is deemed that this research design is acceptable. The procedure of inclusion is organized in such manner that all patients will be informed firstly at inclusion by their treating oncologists and secondly by the data manager. The treating oncologist will spend time explaining the aim of palliative care in general and its specific aim within this study. They will provide an information sheet and an informed consent document to the patient. In a second phase, the data manager will have a consultation of a minimum of half an hour with the patient to explain the nature and procedure of the study in depth and to answer any questions participants might have. The participants will then be asked to give written informed consent and will be given a guarantee that: 1) the data will be treated confidentially, 2) the data will be stored anonymously for analysis later on, 3) study participation will be on a voluntary basis and withdrawal will be possible whenever the patient wishes and 4) non-participation or withdrawing from the study will have no influence on the future care of the patient. After providing informed consent, all patients will fill out the baseline questionnaires in the presence of the data manager so they will be able to request help if necessary. They will also be able to discontinue completing the questionnaire at any moment. Moreover, if they appear to be distressed as a result of filling out the questionnaire, psychologists from the oncology departments will be available to provide counselling.

#### Approval

Approval for this study was given by the Ethical Committee of the Ghent University Hospital, Flanders, Belgium.

## Discussion

The IPaC study is the first randomized controlled single centre phase III trial to implement an early palliative care approach in standard oncological care in the hospital setting in Belgium for patients with advanced cancer. Following a baseline assessment, patients and their informal caregivers will be randomized to either the intervention group where systematic early integration of palliative care will be implemented or to the control group where care will be provided as usual. Follow-up measurements allow the detection of differences in the quality of life, mood and illness understanding between patients in the intervention group and those in the control group.

Our systematic early integration of palliative care intervention is based on the original guidelines of the early palliative care intervention that was examined in the study for non-small lung cell cancer patients but adaptations have been incorporated to fit the specifics of the Belgian health care setting [4]. A first adaptation lies in the fact that the intervention is primarily led by the palliative care team nurses and not by the palliative care physician, due to the organizational structure of hospital-based palliative care in Flanders. The influence of a nurse-led intervention may appear to be less effective than a physician-led intervention but it may be less costly and financially more feasible [5]. A second adaptation is that the palliative care nurse leading the intervention also has a *referring role*. The medical and paramedical members of the oncology team may be able to fulfill the palliative care needs of the patient adequately but their goal often remains to prolong life. Palliative care embraces a different approach, focusing on the needs and expectations of the patient from a holistic point of view, which may lead to the eliciting of different information from the patient and the palliative care nurses who, in this trial, have an important role in referring this information to the oncology team. This interdisciplinary approach will broaden the view on care. A third adaptation consists of the semi-systematic format of consultations based on an interview form in which the important palliative care topics that have to be discussed and treated are listed. In addition, standard symptom assessment (ESAS) is incorporated to evaluate symptom intensity at each consultation and to provide an overview of the fluctuation of symptoms. Research has shown that most health care professionals agree that use of the ESAS enhances patient care because it helps patients in articulating their symptom issues and aids in following them up [29].

Several limitations exist with regards to the IPaC-study. It is a single-centre study in a tertiary hospital setting, which might limit the generalization of the results to other hospitals. On the other hand, the organization of the oncology departments and palliative care team are similar between hospitals in Belgium, having been developed on the basis of the same legislative initiatives. A second limitation is that participants and staff members are not blinded for allocation to the intervention group or control group. It is possible that the treating oncologists and other members of the oncology team are affected by the new approach and will implement the new insights with patients in the control group (crossover effect). However, the oncologists and other health care professionals of the oncology team will be well informed about the goals and design of the study and will be made aware of bias risks. A third limitation concerns the possibility of selection bias, since participants are asked for consent prior to enrollment. Participants more open to end-of-life discussions might be more prone to taking part in the trial than others.

This trial also has several strengths. Firstly, our study protocol consists of a detailed description of standard oncology care, which has a particular focus on providing psychosocial support for cancer patients and their caregivers. Such a description is needed since the organization of standard care has an important influence on this intervention, specifically on the referring role of the palliative care nurses. The inclusion of this explicit description demonstrates a different approach from other early palliative care RCTs. Extensive information has been provided regarding the functioning of the palliative care clinic and the roles of the palliative care clinician in these trials but little information is available concerning the organization of standard oncology care [4, 6–8, 30–32]. In the US, a broad range of supportive services are offered by a multidisciplinary cohort of oncology health professionals but the availability of these services varies greatly among institutions. Hence, extrapolation of this information to the organization of the standard care of the early palliative care trials situated in the US is not feasible [33]. Secondly, for our primary outcome measure we have selected a questionnaire (EORTC QLQ-C30) on quality of life which is used in clinical trials in Europe and has been studied intensively from the perspective of the clinical significance of scores [34].

One of the challenges of the trial is the recruitment of patients with advanced cancer early in the stage of the disease trajectory. A systematic review of early integration of palliative care in hospitals has shown that staff-specific barriers often occur due to the reluctance of physicians to communicate prognostic information to the patient and family and the perception by staff of PC as ‘terminal care’ [35]. Clinicians are often concerned that referral to PC will alarm patients and their informal caregivers [5]. Hence, introducing a clinical trial of PC to advanced cancer patients early in their disease trajectory may prove to be difficult. However, with the support of the head oncologist of each department and the disseminating of the results of previous research in early palliative care we expect that the trial will be successfully initiated in the different departments involved.

## Conclusion

The IPaC trial is a randomized controlled trial approved by the Ethical Committee that aims to assess whether the quality of life of patients with advanced cancer and their informal caregivers is enhanced by implementing systematic early integration of palliative care in a setting where multidisciplinary cancer care is part of standard oncology care. This trial will add to the evidence about the effectiveness of integrated palliative care programmes for cancer patients. We hope that this study will not only show whether systematic early integration of palliative care is effective for cancer patients in Belgium but will also provide an increased understanding of the contribution of the different components of the systematic early integration of palliative care intervention to their quality of life.

## Abbreviations

IPaC: Integration of Palliative Care
US: United Stated
QoL: Quality of Life
PCPs: Palliative Care Programs
RCT: Randomized Controlled Trial
ASCO: American Society of Clinical Oncology
FTE: Full Time Equivalent
ECOG: Eastern Cooperative Oncology Group
ESAS: Edmonton Symptom Assessment Scale
EORTC QLQ C30: European Organisation for Research and Treatment of Cancer Quality of Life Questionnaire
MQOL: McGill Quality of Life Questionnaire
HADS: Hospital Anxiety and Depression Scale
PHQ-9: Patient Health Questionnaire 9
SF-36: Short Form-36 Health Survey
ELDs: End-of-Life Decisions
